
**Follow-Up:**

The subjects will arrive for follow up visits on days 3, 5 & 7 in order to document the odor level.

There will be an interview phone call with the subject's partner (where possible) to assess hers perception of the smell. It will be conducted during days 5-6.

No follow up is required post Removal visit.

1. **Independent Blinded Reviewers (herein: Smellers):**

3 smellers will be chosen to participate in the study to perform a smell test using smell detector device; the "Nasal ranger" device, see the following link for technical information:

[http://www.nasalranger.com/Operations/Nasal%20Ranger%20Operations%20Manual%20v6.2.pdf](http://www.nasalranger.com/Operations/Nasal Ranger Operations Manual v6.2.pdf)

The Smellers will go through a short training in order to know how to operate the device and to assess their skills.

1. **Questionnaire for Subject:**

The subject's own perception of the smell will be documented and graded in VAS of 1-10 and compared to his normal perception of his smell and of the environment perceptive as he sees it.

The subject will also be questioned about his compliance to the required hygiene procedure of his study arm.

1. **Questionnaire for partners:**

The perception of the subject's spouse/partner will be documented where possible, via a phone interview.

## 6.4 Photography

**Photos:**

Photos of the Penis should be taken in each study visit according to the following guidelines:

- - The Camera must have a memory cards sufficient to contain the amount of expected photos of the largest file produced by the camera A spare set of new camera batteries must always be kept in the camera pack
  - A spare camera memory card must always be kept in the camera pack
  - Minimum of 2 photos, 1 from top and 1 from bottom of the glans must be taken presenting 360˚ around the glans and showing the frenulum. It is recommended to take 4 photos from 4 directions around the glans
  - Photos will be taken while a special photo frame is placed around the penis including the subject study number, date of photo, study day, and VAS pain value
  - Photos must be taken with a predefined Digital Camera
  - Camera settings must be on highest definition and resolution
  - Photos must be taken from a fixed distance with predefined lighting
  - Before releasing a subject photos must be verified for quality, specifically –
    - Focus of the photo on the skin surface
    - Lighting
    - Inclusion of subjects data in the photo

At the end of each photo day, all photos must be downloaded to a PC saved in a specific location and backed up on a removable Hard Drive. The Removable Hard Drive must be kept separate from the PC for ensuring no loss of data. Photos must never be erased from the camera digital memory card. In case the card is full a new card will be used and the full card will be saved in a secured location.

7. DeVICE MAINTENENCE AND DISPOSAL

The PrePex device is intended for single use only, device that was removed from the patient should be destroyed by a cutter before disposal to a bio-hazard box.

8. STUDY DESIGN

## 8.1 Study Design

Assessing Odor Level when Using PrePex for HIV Prevention: A Prospective, Randomized, Open Label, Blinded Assessor Trial to Improve Uptake of Male Circumcision.

## 8.2 Sample Size

One hundred (100) subjects scheduled for voluntary circumcision. The subjects will be randomly divided into three balanced study arms: Arm 1, Arm 2 and Arm 3 which will include thirty three (33) subjects respectively.

**Arm 1:** A control arm – subjects instructed to follow the current hygiene instructions of standard washing with soap and water during a daily shower. They will get a soap to take home and will be questioned daily to make sure they followed the cleaning instructions.

They might be requested to wash themselves at the hospital before the actual Removal visit starts.

**Arm 2:** subjects instructed to clean the foreskin with soapy water once a day using a syringe.

They will get a soap and required accessories to take back home and will be questioned daily to make sure they followed the instructions.

Subjects may be requested to wash themselves at the hospital before the actual Removal visit starts.

**Arm 3:** subjects instructed to clean the foreskin with diluted chlorhexidine (1%) once a day using a syringe. They will get chlorhexidine in tubes and required accessories to take back home and will be questioned daily to make sure they followed the instructions.

Subjects may be requested to wash themselves at the hospital before the actual Removal visit starts.

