# Study Synopsis

The PrePex device was accepted for the World Health Organization (WHO) list of prequalified male circumcision (MC) devices and was listed on 31 May 2013.

PrePex became the first medical device for adult male circumcision to receive WHO prequalification as an alternative to the conventional surgical circumcision methods already recognized by WHO.

Voluntary Medical Male Circumcision (VMMC) is a one-time, low cost intervention that shown to reduce men’s risk of HIV infection by approximately 70 percent. The WHO recommends VMMC as part of a comprehensive package of HIV prevention services. The WHO prequalification of PrePex represents an unprecedented opportunity to further the safe and rapid scale up of voluntary medical male circumcision programs [Official statement by the Office of the U.S. Global AIDS Coordinator].

Up to date more than 7,500 MCs were performed using the PrePex device. Rwanda, Zimbabwe and Uganda have completed the WHO clinical roadmap, scientifically validating the safety, efficacy, acceptability and superiority (over dorsal slit, on both measures of time and safety) of PrePex, other countries such as Kenya, Botswana and Mozambique are currently conducting PrePex pilot studies.

A concern that was raised by WHO TAG consulting members regarding the potential acceptability of PrePex by men involved the potential of strong odor extraction from the necrotizing foreskin. PrePex researchers from Rwanda have assumed that there is a possible relation of the level of odor to the personal hygiene and foreskin washing technique. It is speculated that when a patient follows an appropriate washing technique of the foreskin while wearing the device, the odor before device removal (day 7) will be redundant and significantly lower than the odor of the foreskin of a patient that does not follow such washing instructions and technique. Providing scientific evidence of the direct relation between odor and personal hygiene will allow VMMC implementing bodies to create a comprehensive and effective PrePex personal hygiene protocol and increase acceptability of the VMMC.

This clinical study will include the following objectives:

- To compare the different odor levels when examining 3 arms with identical personal hygiene but different foreskin hygiene techniques
- To determine a detailed and validated foreskin cleaning procedure protocol, that will ensure low odor without compromising safety

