**Study arms:**

The subjects will be randomized into 3 study arms, using a randomization table and sealed envelopes:

**Arm 1:** A control arm – subjects instructed to follow the current hygiene instructions of standard washing with soap and water during a daily shower. They will get a soap to take home and will be questioned daily to make sure they followed the cleaning instructions.

They might be requested to wash themselves at the hospital before the actual Removal visit starts.

**Arm 2:** subjects instructed to clean the foreskin with soapy water once a day using a syringe.

They will get a soap and required accessories to take back home and will be questioned daily to make sure they followed the instructions.

Subjects may be requested to wash themselves at the hospital before the actual Removal visit starts.

**Arm 3:** subjects instructed to clean the foreskin with diluted chlorhexidine (1%) once a day using a syringe. They will get chlorhexidine in tubes and required accessories to take back home and will be questioned daily to make sure they followed the instructions.

Subjects may be requested to wash themselves at the hospital before the actual Removal visit starts.

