**Independent Blinded Reviewers (herein: Smellers):**

3 smellers will be chosen to participate in the study to perform a smell test using smell detector device; the "Nasal ranger" device, see the following link for technical information:

[http://www.nasalranger.com/Operations/Nasal%20Ranger%20Operations%20Manual%20v6.2.pdf](http://www.nasalranger.com/Operations/Nasal Ranger Operations Manual v6.2.pdf)

The Smellers will go through a short training in order to know how to operate the device and to assess their skills.

On day 0 pre procedure, the smellers will use the Nasal Ranger device to smell each of the 100 subject's genitals (baseline). Below are the room and procedure requirements. Only after the smelling procedure, will the subject undergo PrePex procedure.

The subjects will arrive to the clinic on days 3, 5 and 7 in order to document their odor levels.

On the Removal day (Day 7), the smellers will attend the Removal procedures and use the Nasal Ranger device. Below are the room and procedure requirements:

- 2 rooms will be used during the study which will have the same constant conditions (same room with no initial smell, same window, same distance from the penis: 30 cm)
- Usage of Nasal ranger device by trained personnel only
- The subjects will be randomized for their turn to enter the room
- When the smeller enters the room, the subject face will be covered and he will not wear his clothes but hospital garment
- After all 100 subjects were smelled by all 3 smellers, the subjects will be randomized again for their turn to enter the room (new randomization)
- When the smeller enters the room, the subject face will be covered and he will not wear his clothes but hospital garment
- The room should be aired between subjects
- The smelling will be always in the same distance from the genitals, by measuring with a ruler, 30 cm distance between the genitals and the end of the "Nasal Ranger"
- Each Smeller will be asked separately to grade the smell as he performs it as it is shown in the "Nasal ranger"
- Only at the end of the smelling procedure will the foreskin and device be removed.

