3. STUDY ENDPOINTS

**Endpoints:**

**Primary Endpoint:**

- The primary endpoint is to assess the different odor levels by evaluating 3 arms of patients with different foreskin hygiene techniques.

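### An optional hospital wash, with no stated method and no requirement to record it, may come between the randomised home cleaning and the day-7 odor reading

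*Protocol*

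**What the plan says.** The arm descriptions appear twice, in the Synopsis (Study arms) and in section 8.2. For Arm 1 the text reads "They might be requested to wash themselves at the hospital before the actual Removal visit starts". For Arms 2 and 3 it reads "Subjects may be requested to wash themselves at the hospital before the actual Removal visit starts". Neither place says who makes the request, on what ground, with what agent or technique, how long before the odor test, or that the wash is recorded.

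The Synopsis section on the blinded reviewers fixes the order of events on that day: "On the Removal day (Day 7), the smellers will attend the Removal procedures and use the Nasal Ranger device", and "Only at the end of the smelling procedure will the foreskin and device be removed". The same section standardises the rooms, the window, the 30 cm distance, the garment, the airing of the room and the order of entry. It does not mention washing.

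The hypothesis, in the Synopsis and again in the Clinical background, is that with a proper washing technique "the odor before device removal (day 7) will be redundant and significantly lower" than without it. The primary endpoint in section 3 names no day: "The primary endpoint is to assess the different odor levels by evaluating 3 arms of patients with different foreskin hygiene techniques". Odor is also read at other visits: "The subjects will arrive to the clinic on days 3, 5 and 7 in order to document their odor levels", plus a day-0 baseline. Section 8.1 describes the study as "A Prospective, Randomized, Open Label, Blinded Assessor Trial".

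**The concern.** The randomised exposure is a cleaning technique and the outcome is odor. An extra wash shortly before the reading acts on the same factor that the arms are meant to vary. It is optional, so some subjects may have it and others not, and the protocol sets no rule for which.

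Three consequences are possible. If the wash is plain soap and water, Arms 2 and 3 receive something close to the control technique just before they are measured. If it is the arm's own technique, the day-7 reading reflects a cleaning prompted at the hospital rather than home use alone. If it is requested more often in one arm, or done differently by arm, the comparison is biased. The smellers' blinding protects the rating itself. It does not protect what happens to the subject before the smellers come in.

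The subject questionnaire asks about compliance with the arm's own procedure, but the text provides for no record of the hospital wash. Without that record, the analysis cannot describe the problem, let alone adjust for it.

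**Working it through.** **Sequence.** Setting the passages side by side gives this order: home cleaning by randomised technique (Study arms; 8.2), possible hospital wash before the Removal visit (same places), odor test by three smellers within that visit, then removal (Independent Blinded Reviewers). A requested wash therefore precedes the day-7 reading.

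**The plan's own figure.** Inputs from section 8.3 are Cohen's d = 0.7, 80% power, 5% level and a two-sample t-test; section 8.3.1 makes tests two-sided.

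- Normal approximation: n per arm = 2(1.96 + 0.842)² / 0.7² = 32.04, rounded up to 33.
- Noncentral t: 33.02 per arm. Power at 33 per arm is 80.0% (81.2% by the normal approximation).

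The stated 33 is reproduced.

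**Dilution (assumed values).** Let f be the average share of the arm difference that the wash removes. For example, f = 0.25 if half the subjects are washed and the wash removes half the difference in those subjects (0.5 × 0.5). Then d_eff = 0.7 × (1 − f), with the SD left unchanged.

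| f | d_eff | t-test power, 33 per arm | n per arm for 80% (normal approximation) |
|---|---|---|---|
| 0 | 0.70 | 80% | 33 |
| 0.10 | 0.63 | 71% | 40 |
| 0.25 | 0.525 | 56% | 57 |
| 0.50 | 0.35 | 29% | 129 |
| 0.75 | 0.175 | 11% | 513 |

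A mixture of washed and unwashed subjects also adds variance. If only the control arm is washed and each washed control subject drops to the treated mean, power is 55% at f = 0.25 and 28% at f = 0.50 (normal approximation). The picture is the same.

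**Bias (assumed values).** Suppose the techniques do not differ, a wash lowers odor by w SD, and two arms differ by Δ in the share washed. The spurious difference is b = wΔ, and the two-sided rejection rate is Φ(b/√(2/33) − 1.96) + Φ(−b/√(2/33) − 1.96).

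| w | Δ = 0.10 | Δ = 0.25 | Δ = 0.50 |
|---|---|---|---|
| 0.35 SD | 5% | 7% | 11% |
| 0.70 SD | 6% | 11% | 30% |

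The nominal rate is 5%.

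**The case against.** Several points on the other side have force.

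- **The wash is only a possibility.** A reader might infer that the day-7 reading is always taken after a wash. The wording permits a wash and does not require one, so this does not follow.
- **No decision-maker is named.** A reader might infer that staff who know the arm choose whom to wash, or send those who smell worst. The trial is open label, so this could happen, but the protocol does not say it. The same permission appears in all three arms, which does not suggest arm-specific use. Bias needs uneven use or methods that differ by arm.
- **The sentence may mean something benign.** It sits in each arm's own description, after that arm's technique and supplies. It can be read as that day's assigned cleaning done on site. That would preserve the contrast and, if everyone did it, align the time since last cleaning. The text allows this reading but does not establish it.
- **Day 7 is not named as the primary time point.** Section 3 gives none, and the wash sentence does not cover the readings on days 0, 3 and 5. That day 7 matters most rests on the hypothesis. A complaint that day 7 is not comparable with earlier days carries little weight, since the primary objective compares arms and the protocol specifies no between-day comparison.
- **The planned model is a repeated measures ANOVA, not a t-test.** This limits the power figures to illustration. It does not remove the problem: a wash is done to the subject, so it shifts all three smellers' readings together and is not averaged out.

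What remains after all this is a discretionary step of unstated method, just before an outcome that it can plainly affect. A wish to equalise hygiene cannot justify the wording, because standardisation needs a fixed rule.

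**Conclusion.** The point holds as a defect in how the protocol fixes the conduct of day 7. A discretionary cleaning, with no stated method and no required record, can come between the randomised technique and the day-7 reading tied to the hypothesis. Even use would mainly dilute the arm difference; uneven use could bias it either way.

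The sequence of events comes from the protocol itself. The size does not: the fall in power from 80% to about 56% or 29% assumes that the wash removes 25% or 50% of the difference, and the false-positive rates assume both a wash effect and an imbalance in its use. The documents give none of these quantities. They therefore do not support saying that the wash erases the difference, that the trial's power is 56% or 29%, or that a biased selection of subjects is planned.

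The point still deserves correction before enrolment, because the effect of an unrecorded wash cannot be removed after the data are collected.

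**What to change.** In the Synopsis (Study arms) and section 8.2, replace the permissive sentence in each arm with one fixed rule, worded identically for all three: no extra hospital wash on day 7 until the three smellers have completed the odor test, including any repeat round that day.

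If the sentence was meant as that day's assigned cleaning done on site, say so. Then require it of every subject, with the arm's own technique and at a fixed interval before the test.

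Under either rule, record any hospital wash and the time since the last cleaning.

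The cost is a wording change in two places and one added data item, with no extra subjects. Under the first rule the smellers may meet unwashed subjects, and any hospital wash has to wait until the odor test is over. The removal procedure itself is not altered.

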## 8.3 Statistical analysis

**Sample size:**

The intention is to obtain at least 100 evaluable subjects under Rwanda ethical responsibility (RNEC), determining to use the most deducted calculation setting and to maintain allocation ratio of 1:1:1 between the 3 study arms (33 per arm).

A sample size for the study was determined based on the two-sample t-test. In order to detect an effect size of 0.7 (Cohen's D) with 80% and at and a 5% level of significance between any two groups a sample size of 33 subjects is required. In the study each subject will have a smell test repeated by three different smellers this will be in order to examine the variability in odor sensation between different clinicians. Given this design and the three groups that will be compared, a statistically more powerful model (repeated measures ANOVA) is used instead of a t-test, and thus the study will be appropriately powered.

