***Statistical Analysis:***

All data will be presented via descriptive statistics. Binary data such as adverse events success/fail criteria will be presented as a count and percentage together with an exact 95% confidence interval. Adverse event rates will be compared descriptively with the reported rates of similar treatments. Continuous data will be represented by a mean, standard deviation, median, minimum and maximum together with 95% confidence intervals for the means.

Study Flow

Screen 120 candidates

100 enrolled subjects

Randomization

Arm 1 -33 subjects

- Standard PrePex
- General hygiene instructions
- Foreskin hygiene general instructions – daily shower

Arm 2 -33 subjects

- Standard PrePex
- General hygiene instructions
- Foreskin specific hygiene instructions – daily soapy water with syringe
- **Follow up visits days 3, 5 & 7**
- Subject questionnaires
- Odor tests by 3 Blinded smellers
- Partner questionnaire – on days 3, 5 & 7
- Removal on day 7
- A random sample of subjects were evaluated a second time on day 7
- Safety - AEs

Arm 3 – 33 subjects

- Standard PrePex
- General hygiene instructions
- Foreskin specific hygiene instructions - daily chlorhexidine with syringe

|  | **Randomization & Screening Visit** | **Applying Visit** |  |  | **Removal Visit** |
| --- | --- | --- | --- | --- | --- |
| **Visit #** | **1** | **2** | **3** | **4** | **5** |
| **Day (D)/week (w)** | **–7 to D0** | **D0** | **D3** | **D5** | **D7** |
| Informed consent | X |  |  |  |  |
| Randomization | X |  |  |  |  |
| Inclusion/exclusion criteria | X |  |  |  |  |
| Medical history & Demography | X |  |  |  |  |
| Current medication including pain killers | X | X |  |  | X |
| Genital examination and potential pictures | X | X | X | X | X |
| Device apply |  | X |  |  |  |
| Foreskin Removal |  |  |  |  | X |
| Device Removal |  |  |  |  | X |
| Subject's subjective pain, tingling and discomfort evaluation |  | X | X | X | X |
| Expected Side effects and AE |  | X | X | X | X |
| Smellers test |  | X | X | X | X |
| Questionnaires for patients & for sub group female partners (between days 5-6) |  |  | X | X | X |
| Statistical analysis of data |  |  |  |  |  |

Table of Contents

[Study Synopsis 2](#__RefHeading___Toc344626056)

[Schedule of Events 8](#__RefHeading___Toc344626057)

[1. Clinical background 12](#__RefHeading___Toc344626058)

[2. STUDY OBJECTIVES AND PURPOSE 15](#__RefHeading___Toc344626059)

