## 4.1Source of Subjects and Enrollment

Male subjects that are voluntary scheduled for circumcision. Only subjects who have signed the last version of an Independent Ethical Committee (IEC)/Institutional Review Board (IRB) approved Informed Consent Form (ICF) and meet all of the eligibility criteria listed below will be qualified for enrollment. The study will recruit at least 100 evaluable subjects who will complete the protocol procedure /treatment and the follow-up schedule.

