## 8.3.1 General Considerations

The primary analysis will be performed on an intent-to-treat basis. Per-protocol analysis also will be performed as a secondary analysis. The required significance level of findings will be equal to or lower than 5%. All statistical tests will be two-sided. Where confidence limits are appropriate, the confidence level will be 95%.

All data will be presented via descriptive statistics. Binary data such as adverse events success/fail criteria will be presented as a count and percentage together with an exact 95% confidence interval. Adverse event rates will be compared descriptively with the reported rates of similar treatments. Continuous data will be represented by a mean, standard deviation, median, minimum and maximum together with 95% confidence intervals for the means.

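### The sample size is computed for a single two-arm t-test, and nothing in the protocol supports the claim that a repeated-measures ANOVA makes the three-arm comparison adequately powered

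*Protocol*

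**What the plan says.** Section 8.3 of the protocol, under Sample size, bases the number on a two-sample t-test; the Synopsis carries the same text under Statistical Considerations. The effect is given as "In order to detect an effect size of 0.7" (Cohen's d), "with 80% and at and a 5% level of significance between any two groups". The word power is missing from that sentence, but 80% can only mean power. The sentence ends with the result, "a 5% level of significance between any two groups a sample size of 33 subjects is required", that is, 33 per arm with 1:1:1 allocation.

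The same paragraph notes that three smellers will assess each subject, to examine how odor sensation varies between them, and that three groups will be compared. It concludes that "a statistically more powerful model (repeated measures ANOVA) is used instead of a t-test, and thus the study will be appropriately powered".

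Section 8.3.1 sets the error level: "The required significance level of findings will be equal to or lower than 5" per cent. It adds: "All statistical tests will be two-sided". The primary objective in section 2 is a comparison of odor across all three arms.

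On numbers, section 4.1 says: "The study will recruit at least 100 evaluable subjects". The Study Flow in the Synopsis shows "100 enrolled subjects".

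**The concern.** The sizing calculation and the named analysis answer different questions. The first covers one pair of arms tested once at 5%. The second is a three-arm comparison. The bridge between them is the assertion that the ANOVA is more powerful, and it comes with no variance component, no correlation between smellers and no power calculation.

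A three-group F-test is not automatically more powerful than a t-test on the two most separated groups. Repeated readings help only to the extent that averaging removes measurement error. Readers of the protocol are told that the trial has at least 80% power for its primary comparison. On the stated inputs the named analysis may have about 70%. A null result would then be read with more confidence than it deserves, and so would the failure of one cleaning technique to separate from another.

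**Working it through.** **Inputs.** From section 8.3: d = 0.7, power 80%, 5% per pair, 33 per arm, three arms, three smellers per subject. From section 8.3.1: two-sided tests, 5% for findings. Not given anywhere: the standard deviation, whether 0.7 applies to one smeller's reading or to the subject's mean, and the between-smeller intraclass correlation (ICC).

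**1. The protocol's own figure.** The normal approximation is n = 2(1.960 + 0.842)² / 0.7² = 32.04, rounded up to 33. For the exact check, the noncentrality is 0.7 × √(33/2) = 2.843 with 64 df and critical value 1.998, which gives power 79.97%. The 33 reproduces. A one-sided test would give 26, so the two-sided reading is the one used.

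**2. What the repeated-measures ANOVA tests between arms.** With every subject read by the same three smellers, the between-arm F is the arm mean square over the subject-within-arm mean square. Both are three times their counterparts in a one-way ANOVA on the subject means, so the ratio is the same, with 2 and 96 df. Relative to a single reading, the variance of a subject mean is multiplied by (1 + 2·ICC)/3. That factor is the only gain the smeller replication can bring.

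**3. Overall F-test with d = 0.7 on the subject-mean scale.** The noncentrality is λ = n Σ(μ − μ̄)² in SD units, and the critical F(2, 96) is 3.091. The largest difference between arms is 0.7.
- Third arm midway (0, 0.35, 0.7): λ = 33 × 0.245 = 8.085, power 70.8%.
- Third arm equal to one end (0, 0, 0.7): λ = 33 × 0.3267 = 10.78, power 83.3%.
- Third arm 0.05 from an end: λ = 10.065, power 80.5%.

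The F-test therefore beats the single t-test only when the third arm sits at or very near one of the other two.

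**4. A pair differing by 0.7, tested at 5% only after a significant F (400,000 simulated trials).** Power is 69.7% with the third arm midway and 76.0% with it at one end. With all arms equal, the chance of any false claim under this rule is 5.0%.

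**5. For contrast, three pairwise tests at 5% with no gate.** With all arms equal, at least one is significant in 12.1% of simulated trials. If the three tests were independent, it would be 1 − 0.95³ = 14.3%.

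**6. If 0.7 is instead on the single-reading scale.** The effect on the mean of three is 0.7 / √((1 + 2·ICC)/3). For the overall F-test with the third arm midway:

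| ICC | Effect on mean | Power |
|---|---|---|
| 1.0 | 0.700 | 71% |
| 0.8 | 0.752 | 77% |
| 0.7 | 0.783 | 81% |
| 0.6 | 0.817 | 84% |
| 0.5 | 0.857 | 88% |

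Power reaches 80% at an ICC of about 0.72.

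**7. Illustrative loss to 30 evaluable per arm (my assumption, about 10%).** The noncentralities are λ = 30 × 0.245 = 7.35 and 30 × 0.3267 = 9.80, so overall power is 66% to 79%. A gated pair has about 65% to 71% by simulation. The single unadjusted t-test has 76%.

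**The case against.** Much of the defence is sound.

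- **The arithmetic is right.** A reader might infer that 33 per arm is a miscalculation. It is not; the number is exact for the test described.
- **No inflated error rate is prescribed.** A reader might infer that the trial will run at about 12% family-wise error. That belongs to three ungated t-tests, which the protocol does not call for. It uses the t-test for sizing and names an ANOVA for analysis, and a three-group F-test at 5% holds 5%. How pairs are tested afterwards may properly be in the analysis plan, so the absence of a procedure here is not the point.
- **Bonferroni is not in the plan.** A pair tested at 0.05/3 would have 65% power, but the documents do not use that procedure, so it does not describe the trial's power.
- **Replication may rescue the power.** Step 6 shows that a moderate ICC would suffice if 0.7 is on the single-reading scale. Odor is also measured at baseline and on days 3, 5 and 7, and using those readings might add precision. The sample-size text mentions only the smellers, so any such gain is unquantified.
- **The recruitment target is a floor.** The protocol wants at least 100 evaluable subjects, and participation lasts up to one week. The box showing 100 enrolled is at most an inconsistency in wording.

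What this does not remove is the inference itself. The protocol concludes adequate power from the choice of model, and it states none of the quantities on which that conclusion depends.

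**Conclusion.** The point holds as a fault in the power statement. The 33 per arm delivers 80% for one unadjusted pair. It has not been shown to deliver 80% for the three-arm analysis that the protocol names. With 0.7 on the subject-mean scale and no gain from baseline or other visits, power is 71% to 83% for the overall test and 70% to 76% for a pair tested after it. The lower figures apply when the third arm lies midway.

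A reader might go further and call the trial underpowered. The documents do not support that. With 0.7 on a single-reading scale and an ICC of about 0.7 or lower, even the midway case reaches 80%. The claim is unsupported, not refuted. Severity is moderate: the stated power needs correcting, while the sample size and the data to be collected stand.

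**What to change.** In section 8.3 and in the matching Synopsis text:

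1. State that the overall F-test across the three arms at 5% is the gate, and that pairwise tests at 5% follow only if it is significant. With exactly three arms this holds the family-wise error at 5%. If all arms are equal, the gate controls it. If only two are equal, there is just one true null pair, and it is tested at 5%.
2. Replace the power statement with about 71% to 83% for the overall test and 70% to 76% for a pair with d = 0.7, at 33 evaluable per arm and assuming no gain from averaging smellers. Alternatively, state the scale of d and the assumed ICC, with its source, and compute the power from those.
3. Delete the closing inference that the study is appropriately powered because an ANOVA is used.
4. Optionally, reconcile the 100 enrolled in the Study Flow with the 100 evaluable in section 4.1, and show the power at an illustrative 30 per arm (66% to 79% overall).

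The cost is wording and a less favourable stated power unless an ICC can be justified. No additional patients are needed.
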